### Sample

#### Prospective RCT

The trial aims to recruit up to 2000 women undergoing a predictive genetic test for a known familial PV in a gene associated with increased risk of breast cancer: *BRCA1, BRCA2, PALB2, CHEK2, ATM, RAD51C* and *RAD51D*. Eligible participants are 18 to 79 years of age, unaffected by invasive or in situ breast cancer or epithelial ovarian cancer, and able to give informed consent and complete online questionnaires in English.

Exclusion criteria include having had previous genomic testing that included polygenic risk information for breast or ovarian cancer and currently undergoing treatment for a cancer diagnosis.

#### Retrospective cohort

To ensure adequate representation of the rarer genes, the trial is inviting up to 400 women who have previously tested positive for a PV in *PALB2, CHEK2, ATM*, *RAD51C* or *RAD51D*. Other inclusion and exclusion criteria are as for the prospective RCT.

### Recruitment

#### Prospective RCT

Potential participants are identified by the individual FCCs following referral for predictive testing for a PV detected in a genetic relative. The managing FCC directs eligible patients to the PRiMo online information and consent platform where they can complete the consent form prior to or within 1 day following the standard pre-test counselling appointment with the FCC where the GHP will confirm their willingness to participate and answer questions.

#### Retrospective cohort

Potential participants are identified from the databases of the FCCs and sent an invitation letter or email inviting them to access the PRiMo online information and consent platform. Individuals who complete the consent form are phoned by a GHP or researcher to verbally re-confirm their understanding and willingness to participate and to organise their FCC results appointment. Individuals not interested in the study are asked to return the decliner response form and non-responders may be followed up by the FCC.

#### Online information and consent platform

The PRiMo online information and consent platform uses REDCap (Research Electronic Data Capture) tools, a secure, web-based software platform designed to support data capture for research studies.^33 34^ On accessing the platform, potential participants are provided with information specific to the prospective and retrospective groups and then an online version of the detailed participant information sheet. Interested individuals provide basic information, complete screening questions to confirm eligibility and electronically sign the consent form. The consent form allows participants to ‘opt out’ of being invited to participate in the qualitative interviews and focus groups, and provides participants with the option to consent to their data and samples being included in other closely related future research projects that have been approved by a Human Research Ethics Committee. Following the pre-test counselling appointment or phone call, participants are provided with a separate online optional consent form that provides permission for the researchers to access their data from the Australian Government Medicare Benefits Schedule (MBS) and Pharmaceutical Benefits Scheme (PBS).

### Genomic analysis and PRS

The predictive test is performed by the accredited molecular diagnostic laboratory for each FCC independently of the study and the standard clinical test report is provided to the FCC and the central study team. An additional aliquot of the DNA sample is provided by the diagnostic laboratory for the research genomic analysis.

SNP genotyping is performed on a custom Illumina GSA array. Quality control and genotype calling of the array data are performed using standard bioinformatic packages. Missing genotypes, either due to limitations of the array or issues arising from individual samples, are managed by imputation against the TOPMED and 1000 Genomes whole-genome data sets using standard methodology to optimise the imputation accuracy for each SNP.

Calculation of a breast cancer PRS (BCAC-313) and ovarian cancer PRS (OCAC-36) and generation of the report are performed by the central study team using standard methods developed in the pilot study.^21 22^ Ancestry information is incorporated into the breast cancer risk prediction; information on self-reported ethnicity and published figures on the characteristics of the BCAC-313 PRS score specific to different ancestral groups^25 35 36^ to provide an adjusted Z-score for incorporation into the multifactorial assessment.

### Randomisation

Randomisation occurs following completion of the pre-test counselling appointment and pre-result baseline questionnaire. Participants in the prospective RCT are randomly assigned to either standard care or PRiMo intervention with a 1:1 allocation as per a computer-generated simple randomisation schedule using the REDCap randomisation module. The trial staff allocating participants do not have access to the randomisation schedule.

To minimise discrepancies in risk advice provided to relatives managed by the same FCC, only the first participant in a family at that site will be randomly assigned to either standard care or intervention. Any related participants that attend the same FCC will be allocated to the same group. Participants will not be informed of this procedure and potential participants will not be aware of their group prior to enrolment.

Given the nature of the intervention, participant and clinician blinding is not possible and both the participant and their FCC will be informed of the outcome following allocation, and procedures for unblinding are not required. Analysis of the primary study aims will be performed without knowledge of the intervention status of each group.

Participants in the retrospective cohort will not be randomised and all will receive the intervention.

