### Statistical considerations and sample size

A power calculation was performed based on the frequency of cancer risk management events in cases and controls—including uptake of recommended strategies and reduction in strategies no longer recommended based on the participants’ risk assessment. Significance is set at p≤0.05 for independent direct comparisons of the two arms, and p≤0.01 after correction for multiple testing for comparisons between subgroups (gene positive; gene negative; and high, moderate and population risk). In the prospective enrolment group, the sample size has power to detect 10% differences in proportions between arms (power for χ^2^ test exceeds α≤0.05, β≥0.8 at 85% of enrolment of prospective group) and power to detect 25% differences in the smallest risk subgroup (moderate risk), accounting for multiple testing. Comparison of the prospective accuracy of PRiMo vs standard care risk assessments was based on a model of the expected distribution of genetic testing results and the PRS that projected an expectation of incident cancers in follow-up. At 3 years mean follow-up, the full sample will be powered to detect a 10% increase in the proportion of breast cancers detected in the high-risk group; that is, a greater proportion of the breast cancers detected in follow-up will occur in the high-risk women in the intervention arm than in the standard care arm (β=88%, α=0.05, on a test for superiority). The sample for retrospective recruitment was based on the number of families with an identified PV in *PALB2*, *ATM* or *CHEK2* in Australia.

For the secondary aims, the proposed study size correlates to more than adequate statistical power (β>90%, α=0.01) to detect differences in the questionnaire outcomes. Consideration will be given to both the statistical and clinical significance of any differences.

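### Later relatives take an arm the recruiting clinic can already know, so a first-in-family sensitivity analysis and a family-clustered test of proportions should be pre-specified

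*Protocol article*

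**What the plan says.** **Allocation** (Protocol article, Randomisation). Women are assigned "with a 1:1 allocation as per a computer-generated simple randomisation schedule", but only the first participant from a family at a site goes through it. For the others: "Any related participants that attend the same FCC will be allocated to the same group". The stated reason is to avoid conflicting advice among relatives seen at one clinic.

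**Safeguards** (same section). "The trial staff allocating participants do not have access to the randomisation schedule". Participants are not told of the family rule and do not know their group before enrolling. The primary aims are analysed masked to group. The section also says that "both the participant and their FCC will be informed of the outcome following allocation".

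**Recruitment** (Recruitment, Prospective RCT). "The managing FCC directs eligible patients to the PRiMo online information and consent platform", and its staff check at pre-test counselling that the woman wants to take part.

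**Power** (Statistical considerations and sample size). "Significance is set at p≤0.05 for independent direct comparisons of the two arms", and "the sample size has power to detect 10% differences in proportions between arms". The test named is chi-square, with at least 80% power at 85% of prospective enrolment. No design effect is mentioned. A separate comparison of cancers arising in the high-risk group is given 88% power in the full sample.

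**Analysis** (Data analysis, Quantitative analysis). Proportions are referred back to what was set out earlier. The same paragraph then lists family among the levels of clustering, to be handled by a linear mixed model or GEE.

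**The concern.** Once the first member of a family has been allocated, the arm of every later relative at that clinic is fixed, and the clinic has been told it. The same clinic then steers those relatives towards consent. This is cluster allocation with recruitment after allocation. Hiding the schedule does not protect these women, because their arm does not come from it. Keeping participants unaware closes one route and leaves the recruiting staff's route open.

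If families in the PRiMo arm are approached more readily, or their relatives encouraged differently, the arms can come to differ in age, carrier probability or motivation. These bear directly on uptake of risk management. Masking the analyst comes too late to help, and a mixed model or GEE corrects the variance, not the selection.

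There is also a smaller question of precision. The only test of proportions named is an unadjusted chi-square test, while the analysis section offers a clustered model. The article does not say which governs the between-arm comparison of proportions.

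**Working it through.** **1. Can the arm be known before consent?** Set the rules side by side: the first member is randomised; the clinic learns the result; a later relative at that clinic gets the same arm; the clinic directs her to consent. For any relative recruited after the first member's allocation, the answer is yes. A relative who consents before then is not affected. The schedule safeguard and the participant safeguard do not touch this sequence.

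**2. How would selection reach the estimate?** If relatives make up a similar share of each arm, the bias in the all-participant difference is roughly (share of relatives) × (difference between arms that selection creates among relatives). The article gives neither term, so no figure follows.

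**3. The plan's own power figure.** Inputs: "The trial aims to recruit up to 2000 women"; 85% of 2000 = 1700, or 850 per arm; 10 points read as an absolute difference; two-sided α = 0.05 (sidedness not stated). No baseline proportion is given, so baselines from 5% to 85% were scanned. The worst case is 45% v 55%.

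Power = Φ{[0.10√n − 1.96√(2 × 0.5 × 0.5)] / √(0.45 × 0.55 + 0.55 × 0.45)}

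At n = 850: (2.916 − 1.386)/0.7036 = 2.17, so power is 0.985. The stated bound of at least 0.80 is confirmed; 80% power needs at most 392 per arm (784 in all).

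**4. First-in-family women only, 10-point comparison, from 1700.**

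| First-in-family share | Per arm | Power |
|---|---|---|
| 80% | 680 | 0.959 |
| 70% | 595 | 0.933 |
| 60% | 510 | 0.893 |
| 50% | 425 | 0.832 |

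The break-even share for 80% power is 784/1700 = 46%.

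**5. Clustering, all women.** Family size m and intraclass correlation (ICC) are not given. With equal families the design effect is DE = 1 + (m − 1) × ICC. Assumed examples: m = 2, ICC 0.1 gives 1.10; m = 1.5, ICC 0.5 gives 1.25; m = 2, ICC 0.5 gives 1.50. The type I error of an unadjusted test is 2{1 − Φ(1.96/√DE)}. The power of a clustered test uses n = 850/DE.

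| DE (assumed) | Type I error, unadjusted | Power, clustered test |
|---|---|---|
| 1.10 | 0.062 | 0.976 |
| 1.25 | 0.080 | 0.959 |
| 1.50 | 0.110 | 0.921 |
| 2.00 | 0.166 | 0.832 |

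A clustered test keeps 80% power up to DE = 850/392 ≈ 2.17.

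**6. The 88% accuracy comparison.** By normal approximation, 88% power at two-sided 0.05 means a standardised effect of 1.96 + 1.175 = 3.135. If cancers fall in proportion to women, restricting to a share s gives power Φ(3.135√s − 1.96):
- s = 0.7: Φ(0.66) ≈ 75%
- s = 0.5: Φ(0.26) ≈ 60%
- 80% power needs s = (2.80/3.135)² ≈ 0.80

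For all women with a clustered test, replace s by 1/DE: about 85% at DE 1.1, 80% at 1.25 and 73% at 1.5.

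**7. Moderate-risk subgroup.** Detecting 25 points at α = 0.01 needs up to 92 per arm before any design effect. The subgroup size is not stated, so its headroom cannot be checked.

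**The case against.** **The analysis already accounts for families.** A reader might infer from the chi-square power calculation that the trial will analyse relatives as independent women. The article does not support that. Its analysis section names family as a cluster level and plans a mixed model or GEE, in the same paragraph as the risk-management endpoints. What stands is an ambiguity about proportions, which an analysis plan not shown here may settle.

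**The family rule has a purpose.** Avoiding discrepant advice within a family is a sound reason, and nothing here argues for dropping it. The article also plans to compare participants with decliners and the groups with each other, which could reveal imbalance. Those comparisons are not said to separate randomised women from assigned relatives.

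**No bias has been shown.** This is correct. The article says the clinic directs eligible patients; it does not describe clinics choosing among relatives. The gap is one of opportunity.

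**First-in-family should not become the primary analysis.** A reader might infer from the ample power of the 10-point comparison that restricting every analysis would cost nothing. Step 6 shows otherwise: the accuracy comparison would fall below 80% power unless about 80% of the sample is first-in-family. Restriction also discards enrolled women and changes the population analysed. This objection stands, and it limits the remedy to a sensitivity analysis.

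**The type I error range is assumed.** This also stands. Carrier status can differ within a family, and clusters exist only within one clinic, so the design effect may be small.

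**Conclusion.** The concealment gap is real and follows from the allocation and recruitment rules as written: a later relative's arm can be known to her recruiters before she consents, and no stated safeguard or planned model removes the selection that could result. Its effect on the estimate cannot be sized, because the number of relatives is not reported.

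The clustering point is narrower. The article should say which method governs the tests of proportions. If the unadjusted test were used, its type I error would be about 6% to 11% at assumed design effects of 1.1 to 1.5.

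The 10-point comparison can afford both remedies: about 83% power in first-in-family women at a 50% share, and at least 80% for a clustered test up to a design effect of about 2.2. That does not extend to the 88% accuracy comparison, and it cannot be checked for the subgroup. This is an inexpensive improvement, not a defect that undermines the trial.

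**What to change.** Keep the family rule and the all-participant primary analysis. Then:

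1. Pre-specify, as the key sensitivity analysis, the between-arm comparison restricted to women who were themselves randomised (first in family at their clinic).
2. Report, by arm, how many relatives were approached and how many enrolled, with their baseline characteristics shown apart from those of the randomised women.
3. State that between-arm tests of proportions use the family-clustered model of the Quantitative analysis section, and that the chi-square test served only for the power calculation.
4. Give the assumed family size and ICC, or the observed values once enrolment is known, and restate power for the 88% comparison and the moderate-risk subgroup with that design effect.

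**Cost.** Some analysis-plan wording and one extra analysis, with no new participants. A marker separating randomised from assigned women is needed. The article does not describe one, though applying the family rule requires knowing who was first. Counts of relatives approached depend on clinic records. Intervals will be wider in the sensitivity analysis, and for the accuracy comparison it should be read as supportive unless about 80% of women are first-in-family. The clinic's foreknowledge itself remains; the sensitivity analysis only takes its effect on later relatives out of that estimate.

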### Study outcome measures and data collection

The data collection timetable is depicted in figure 2 showing the outcomes comparisons that will address the primary and secondary aims.

**Figure 2 F2:**
[figure not shown]
Timetable of data collection for primary and secondary study aims.

#### Quantitative data

Data will be collected before participants attend their FCC to receive their genetic test results, risk assessment and risk management advice (pre-result) and at set timepoints after their results, as outlined in table 1.

**Table 1 T1:** Participant questionnaires and clinical data collection at each timepoint

	Timepoint						
	Pre-result	Post-result					
		1 month	6 months	1 year	Crossover*	2 years	3 years
Participant questionnaires							
Demographic data	X						
Risk factors: lifestyle, personal, reproductive, medical and medications	X			X		X	X
Risk management intentions		X			*X*		
Risk management uptake				X		X	X
Cancer events	X		X	X		X	X
Quality of life and psychosocial instruments:							
Assessment of Quality of Life (AQoL)−8D^40^	X	X	X	X	*X*		
Cancer risk perception^43^	X	X	X	X	*X*		
Cancer Worry Scale (CWS)^44^	X	X	X	X	*X*		
Genomics Outcome Scale (GOS)^45^	X	X			*X*		
List of Threatening Experiences (LTE)^46^	X	X	X	X	*X*		
Feelings About genomiC Testing Results (FACToR)^47^		X	X	X	*X*		
Post-traumatic Growth Index - Short Form (PGI-SF)^48^		X	X	X	*X*		
Psychological Adaptation to Genetic Information Scale (PAGIS)^49^		X	X	X	*X*		
Personal Utility of Genomic Results (PrU)^50^		X	X	X	*X*		
Clinical data collection							
Risk factors: family cancer history (pedigree) and PV predictive test report	X						
Risk assessment and risk management recommendations		X			*X*		
Medicare Benefits Schedule (MBS) and Pharmaceutical Benefits Scheme (PBS) claims (optional consent)							X

* One month post-second results appointment for standard care arm participant that has chosen to receive PRiMo intervention (crossover).

PVpathogenic variant

#### Qualitative data

Qualitative interviews (up to 60) complement and triangulate the psychosocial questionnaire data with the sample purposefully selected to cover a range of risk and demographic profiles. The first interview will occur 1 to 4 months after result disclosure and a second interview conducted at about 12 months. The recorded, semistructured interviews (45 to 60 min) will be conducted by a trained psychosocial researcher, covering the experience of receiving personalised risk information (motivation for genetic testing, expectations and understanding of information); risk perception and management strategies planned or undertaken; the impact of results and changes over time; and (dis)advantages of participation.

Semistructured focus groups will be conducted with approximately 5–30 participants (3 to 8 per group) to explore perspectives towards the future implementation of PRS for breast/ovarian cancer risk assessment in clinical genetics, including barriers and enablers. To achieve a representative sample, participants will be purposefully recruited to reflect the range of age, genetic result and cancer risk. Focus groups will be moderated by a trained researcher using a guide informed by two validated implementation determinant frameworks.^37 38^

### Statistical considerations and sample size

A power calculation was performed based on the frequency of cancer risk management events in cases and controls—including uptake of recommended strategies and reduction in strategies no longer recommended based on the participants’ risk assessment. Significance is set at p≤0.05 for independent direct comparisons of the two arms, and p≤0.01 after correction for multiple testing for comparisons between subgroups (gene positive; gene negative; and high, moderate and population risk). In the prospective enrolment group, the sample size has power to detect 10% differences in proportions between arms (power for χ^2^ test exceeds α≤0.05, β≥0.8 at 85% of enrolment of prospective group) and power to detect 25% differences in the smallest risk subgroup (moderate risk), accounting for multiple testing. Comparison of the prospective accuracy of PRiMo vs standard care risk assessments was based on a model of the expected distribution of genetic testing results and the PRS that projected an expectation of incident cancers in follow-up. At 3 years mean follow-up, the full sample will be powered to detect a 10% increase in the proportion of breast cancers detected in the high-risk group; that is, a greater proportion of the breast cancers detected in follow-up will occur in the high-risk women in the intervention arm than in the standard care arm (β=88%, α=0.05, on a test for superiority). The sample for retrospective recruitment was based on the number of families with an identified PV in *PALB2*, *ATM* or *CHEK2* in Australia.

For the secondary aims, the proposed study size correlates to more than adequate statistical power (β>90%, α=0.01) to detect differences in the questionnaire outcomes. Consideration will be given to both the statistical and clinical significance of any differences.

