## Introduction

 The hereditary component underlying breast and ovarian cancer risk is one of the highest for any solid tumour, meaning that women at highest risk can be identified through genetic testing combined with personal and family risk factors, using validated risk assessment tools.^1 2^ A highly effective way to prevent breast cancer deaths is to target risk management strategies to those at higher risk. At the high end of familial risk, genetic testing is well-established for rare pathogenic variants (PVs) in a panel of breast cancer genes.^3^ The best known are *BRCA1* and *BRCA2* which convey average lifetime breast cancer risks of 50% to 70% and significant risks for ovarian cancer and other malignancies.^4^

For women who carry a PV in *BRCA1* or *BRCA2,* evidence shows that risk management options, including screening from a young age, breast MRI screening, risk-reducing medication and prophylactic mastectomy and oophorectomy, are effective.^5^ The current panel of genes with strong evidence for use in clinical practice include *PALB2, CHEK2*, *ATM*, *RAD51C* and *RAD51D* with additional genes such as *BARD1* (breast cancer) and *BRIP1* (ovarian cancer) continuing to emerge. Notably, with the exception of *PALB2*,^6^ the breast cancer risk for these more recently described genes is substantially lower than for *BRCA1* and *BRCA2* and they are commonly described as moderate risk genes (risks twofold to fourfold compared with the population). The clinical model developed over years to manage the clear high risks of *BRCA1* and *BRCA2* has had to adapt to the complexity introduced by greater clinical uncertainty from both the less mature evidence and the more moderate risks associated with the recently identified genes. However, genetic testing, including all of these genes, is now a standard part of breast cancer care.^7^

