### Design and setting

The PRiMo intervention is being evaluated using a two-arm superiority multicentre RCT. Study participants will be recruited through 11 dedicated FCCs around Australia where unaffected women are referred for predictive genetic testing of high-risk or moderate-risk breast or ovarian cancer genes, following detection of a likely pathogenic (class 4) or pathogenic (class 5) variant in a family member. Participants in the RCT are allocated to either (i) a standard care group, who undergo predictive testing as per the FCC’s usual practice or (ii) an intervention group, where the genetic healthcare provider (GHP) at their FCC provides them with risk assessment and management advice based on the PRiMo risk assessment, which integrates their rare PV genetic test result, breast and ovarian cancer PRS, detailed family history information and personal risk factors. Based on consumer input the study design allows participants in the standard care group to crossover and receive their PRiMo risk assessment including the PRS, 1 year after their standard results appointment so that this is eventually available to all participants.

Although comparatively rare, PVs in breast cancer predisposition genes other than *BRCA1* and *BRCA2* are of particular interest given that in this context, the PRS results can have increased implications for risk stratification. To ensure adequate representation of these genes, the study will also recruit a retrospective cohort of women who have previously been found to carry a PV in one of these genes. These participants will be provided with updated risk management advice from a GHP at their FCC based on the PRiMo risk assessment.

The study opened at the first site in July 2021 and is expected to take at least 5 years including recruitment and follow-up. Figure 1 summarises the study procedures for the prospective RCT and the retrospective cohort.

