## Ethics and dissemination

Ethics approval was granted by the Peter MacCallum Cancer Centre Human Research Ethics Committee (Melbourne, Victoria, Australia) in November 2020 (HREC/64060/PMCC). Research governance authorisation at each site was established prior to recruitment initiation. The trial is sponsored, and may be audited, by the Peter MacCallum Cancer Centre. Protocol modifications are approved by the ethics committee and sponsor (current approved protocol is v3.4 dated 8 November 2023). The sponsor and funder have no direct involvement in study design, data collection, analysis or decisions to publish the data. All participants are required to provide informed consent and individuals will not be identifiable in study reports or publications. Enrolment began in June 2021 and is expected to end in January 2025. Study participants may receive brief updates on the trial progress with their annual questionnaires and will receive an electronic summary of the study findings once the trial is completed. The trial is registered on the Australian New Zealand Clinical Trials Registry ACTRN12621000009819.

The trial data and implementation aims of the study are intended to be aligned with similar programmes internationally.^42^ The results of the PRiMo trial will be disseminated through peer-reviewed publications and presentation to the scientific community, and contribute to the international effort to understand how best to use this information to improve patient care.

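### The stated 88% power for the between-arm comparison of breast cancers in the high-risk group cannot be obtained from the number of cancers the trial can be expected to yield

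*Protocol article*

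**What the plan says.** The section Statistical considerations and sample size gives a power statement for the prospective accuracy of the two kinds of risk assessment. At a mean follow-up of 3 years, it says, "the full sample will be powered to detect a 10% increase in the proportion of breast cancers detected in the high-risk group". The next clause fixes the contrast: a greater share of the cancers "will occur in the high-risk women in the intervention arm than in the standard care arm". The operating characteristics are "β=88%, α=0.05, on a test for superiority", where β can only mean power. Sidedness is not given. The section says that a model projected the incident cancers, but prints neither their number nor the standard-care share.

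The other inputs are elsewhere in the article. Under Prospective RCT: "The trial aims to recruit up to 2000 women undergoing a predictive genetic test". Under Randomisation, allocation is 1:1, and the retrospective cohort (up to 400 women) is not randomised and all receive the intervention. The strengths and limitations list says that women testing positive and women testing negative are both included. The Introduction describes *BRCA1* and *BRCA2* as genes "which convey average lifetime breast cancer risks of 50% to 70" percent.

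**The concern.** A share of cancers has cancers as its denominator. About 1000 women per arm is a large sample for a proportion of women, but unaffected women followed for about 3 years produce few breast cancers, and those cancers are all the information this test has. The printed power would fit several hundred cancers per arm, or a different test.

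The Aims section makes accuracy and calibration of the risk assessment part of the primary aim, in the medium to long term. If the comparison is reported against a stated 88% power, a non-significant result will carry more weight than the number of cancers can support.

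**Working it through.** **1. Can the 88% be reproduced?** Not directly, because the projected cancers and the baseline share are not printed. The check is therefore whether any reasonable values of them give 88% for the test as worded.

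**2. Cancers needed per arm.** Two-proportion test with pooled variance, p₂ = p₁ + 0.10 and p̄ the mean of the two:

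n = [z_α√(2p̄(1−p̄)) + z_0.88√(p₁(1−p₁)+p₂(1−p₂))]² / (p₂−p₁)²

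Here z_α = 1.960 two-sided or 1.645 one-sided, and z_0.88 = 1.175. For 80% vs 90%, two-sided: (1.960×√0.255 + 1.175×√0.25)²/0.01 = (0.990 + 0.587)²/0.01 ≈ 249.

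| Standard care vs intervention share | Two-sided | One-sided |
|---|---|---|
| 40 vs 50%, or 50 vs 60% | 485 | 392 |
| 60 vs 70% | 445 | 360 |
| 70 vs 80% | 367 | 297 |
| 80 vs 90% | 249 | 201 |
| 85 vs 95% | 175 | 141 |

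Reading the 10% as a relative increase needs more cancers, for example about 411 per arm two-sided for 80% vs 88%.

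**3. Cancers available.** 2000 women × 3 years = 6000 woman-years at most. Convert lifetime risk to an average annual hazard as −ln(1−risk)/years, spread over 60 years (assumption):

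- 50%: 0.693/60 = 1.16% per year
- 70%: 1.204/60 = 2.01% per year
- 14.3%, which the Introduction treats as close to the population level and which is used here for non-carriers: 0.154/60 = 0.257% per year

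Assume half are carriers, all at *BRCA* level. This is generous, because moderate-risk genes are also enrolled. Risk-reducing surgery and loss to follow-up are ignored.

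- Low: 3000×1.16% + 3000×0.257% ≈ 42 cancers, 21 per arm
- High: 3000×2.01% + 3000×0.257% ≈ 68 cancers, 34 per arm

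Upper bound, with all 2000 women carriers at 70%: 6000×2.01% ≈ 120 cancers. Over 50 years instead of 60 the hazard is 1.204/50 = 2.41% per year, giving about 144. That is 60–72 per arm.

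For comparison, 80% vs 90% two-sided needs 2×249 = 498 cancers in 6000 woman-years, or 8.3% per year across all women, non-carriers included.

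**4. Power at those counts.** Power = Φ{[0.10 − z_α√(2p̄(1−p̄)/n)] / √[(p₁(1−p₁)+p₂(1−p₂))/n]}. For 80% vs 90% at n = 34, two-sided: (0.10 − 1.960×0.0866)/0.0857 = −0.81, so power is 21%. Entries are two-sided / one-sided:

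| Shares | 21 per arm | 34 per arm | 60 per arm | 72 per arm |
|---|---|---|---|---|
| 50 vs 60% | 9 / 16% | 13 / 21% | 19 / 29% | 22 / 33% |
| 60 vs 70% | 10 / 17% | 14 / 22% | 21 / 31% | 24 / 35% |
| 70 vs 80% | 11 / 18% | 16 / 24% | 24 / 35% | 28 / 40% |
| 80 vs 90% | 14 / 23% | 21 / 31% | 33 / 46% | 39 / 51% |
| 85 vs 95% | 19 / 28% | 28 / 39% | 45 / 57% | 52 / 64% |

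**5. Wider assumptions.** With 40–60% carriers, 1.0–2.5% per year in carriers and 0.2–0.3% in non-carriers, the total is 31–97 cancers (16–49 per arm). Over 15–50 per arm and shares of 50–85%, power is 8–38% two-sided and 14–51% one-sided.

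**6. Counting the retrospective cohort.** 400×3×2.01% ≈ 24 further cancers in the intervention arm gives 34 vs 58. At 85% vs 95% power is 39% two-sided and 50% one-sided.

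**7. Nearest approach to 88%.** 90% vs 100%, one-sided, with 72 cancers per arm gives 87%. It requires every woman to be a carrier at the top of the quoted risk and every intervention-arm cancer to be classed high-risk.

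**The case against.** The strongest reply is that the calculation rests on a model that the article only mentions, as a condensed article may, so an outsider cannot call the figure wrong. It is true that the missing inputs are not themselves a fault, and that every power value above depends on assumed inputs. A reader might infer that the design has a fixed power of 10–30%. The documents do not support so narrow a statement, because carrier share, incidence, baseline share and sidedness are all unprinted. But the conclusion does not need them: making every woman a top-risk carrier still leaves the test as worded far short of 88% for baseline shares of 50–85%.

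A second reply is that another test was meant. This has force. A paired comparison of both assessments on about 75 cancers, with 10% reclassified in one direction only and a one-sided test, gives 88%. A one-sample test of 85% vs 95% on 75 cancers, one-sided, gives 90%. So the sponsor's number may be sound for a different analysis. The article nevertheless describes arm against arm, and for that comparison the figure does not hold.

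A third reply is that the full sample may include the retrospective women. They are not randomised and add no standard-care cancers. Step 6 shows that including them does not restore 88%.

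**Conclusion.** The point stands in this form: for the between-arm comparison that the article describes, 88% power is not attainable from the expected cancers. On the article's lifetime risks with half carriers, power is about 9–28% two-sided or 16–39% one-sided. At the upper bound of 60–72 cancers per arm it is no more than 52% or 64%. Both ranges assume standard-care shares of 50–85%, a constant hazard over 50–60 adult years, no risk-reducing surgery and no loss.

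Two further inferences are tempting but not supported:

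- **That a 3-year mean is unattainable.** The study is "expected to take at least 5 years including recruitment and follow-up", which is a minimum, and enrolment "is expected to end in January 2025". A later close would bring the mean close to 3 years, and the shortfall under a 5-year close would hardly change the power.
- **That the trial can detect only some single difference, such as 30 points.** At baselines of 80–85% there are no 30 points left above the baseline, so no one figure applies.

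Nor does the finding show that the trial is too small overall. The separate power statement for risk-management events has women as its unit and is not touched by this argument.

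**What to change.** In Statistical considerations and sample size, state four inputs for this comparison: the projected breast cancers per arm, the assumed share in the high-risk group under standard care, whether the test is one- or two-sided, and the test itself. State also whether the 10% is absolute or relative, and write the 88% as power, not as β. Then take one of three routes:

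- Replace the 88% with the power, or the detectable difference, that those inputs give for the between-arm test.
- If the 88% came from a paired, one-sample or other comparison, describe that comparison in place of arm against arm.
- Otherwise label the between-arm comparison as descriptive and report the difference in shares with a confidence interval.

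The cost is wording only. A stated figure may become less favourable; no extra participants are needed.
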